### Characteristics of participants

#### Inclusion criteria

Adult patients with confirmed diagnosis of bronchial asthma visiting one of the 20 participating practices will be included consecutively. All patients had been diagnosed with asthma by a pulmonologist according to defined criteria. Patients are eligible for inclusion if they have not yet attended an asthma education program or have not attended such program within the past ten years. Patients must also declare their written informed consent to participate in the study.

#### Exclusion criteria

Patients with the following criteria will be excluded:Patients not agreeing to the studyPatients under the age of 18 years due to legal groundsPatients not having sufficient knowledge of German as the online education program is currently only available in GermanPatients whose asthma education dates back ≤ ten years

### Interventions

Patients’ schedule of enrolment, interventions and assessments is summarized in Figure 2.

**Fig. 2 Fig2:**
[figure not shown]
Standard Protocol Items: Recommendations for interventional trials (SPIRIT) schedule. eAEP implies electronic asthma education program; AKT, asthma knowledge test; ACT, asthma control test; API, autonomy preference index; FU, follow-up; t_0_, time point 0 (baseline assessment); t_1_, time point 1 (two weeks after study inclusion); t_2_, time point 2 (three-month follow-up); t_3_, time point 3 (six-month follow-up)

#### Intervention Group

Patients from general practices in the intervention group will receive access to the eAEP. Patients will also obtain a peak flow meter and an asthma diary from their GP in advance. The use and application of these tools is addressed in the eAEP. The eAEP consists of a webpage and is available at www.asthmaselbstmanagement.de. It is intended that patients work through the eAEP independently at home using a PC or notebook. The eAEP encompasses an introductory page, four chapters including a short quiz at the end of each chapter, a final quiz after completing the courses as well as a glossary with frequently asked questions. Chapter one conveys basic knowledge on bronchial asthma as a chronic disease. Furthermore, it provides information on the structure and function of the respiratory tract. In chapter two, patients will be taught about asthma medication and its application. Chapter three is about self-management and focuses on the application of an asthma diary, an asthma action plan, as well as the peak flow measurement. The last chapter provides information on how to behave during an asthma emergency. After completing the four chapters, patients’ asthma knowledge will be tested in the final quiz and feedback on their performance for sufficient learning will be provided. If asthma patients answered fewer than 80 percent of the questions correctly, they will be advised to work through the courses again.

Patients do not enter any personal data when performing the eAEP. Furthermore, there is no documentation on how often and for how long the website was accessed. In total, two to three hours are estimated for the complete and conscientious use of the program.

The eAEP is based on the structured and evaluated fAEP of the Bad Reichenhall clinic in Germany. The eAEP was developed by a pneumologist with long-time experience in patient education [name] and a general practitioner [name]. Both developers are members of the national asthma guideline board [2].

Three weeks after study enrolment, patients in the intervention group will attend the follow-up appointment in the general practice to ensure that the content of the eAEP had been understood correctly as well as to ensure patient safety. By using the “physician-patient-appointment” questionnaire, GPs will test patients’ asthma knowledge (see section ‘Measurements’).

#### Control Group (usual care)

Patients from general practices in the control group will receive care as usual according to guideline recommendations. This encompasses either a referral to a pulmonary practice for structured fAEP or a structured fAEP in a certified general practice. Patients will be asked to attend the fAEP within twelve weeks. Furthermore, patients in the control group will also receive a peak flow meter and an asthma diary in advance.

Twelve weeks after study enrolment, patients in the control group will visit the general practice again to discuss remaining questions as well as to test patients’ asthma knowledge on the basis of the “physician-patient-appointment” questionnaire. At the end of the study, patients of the control group will also receive access to the eAEP.

### Measurements

#### Physician documentation at baseline assessment (time point 0 (t_*0*_))

After obtaining written informed consent, the respective physician will provide information on current asthma medication of the patient as well as asthma symptoms over the past four weeks. In addition, lung function in terms of FEV_1_ and FEV_1_/FVC will be assessed by performing a spirometry or respective parameters will be extracted from the patient chart (see Additional file 1 for further details).

#### Patient questionnaire at baseline assessment (t_*0*_)

Immediately after inclusion in the study, patients will be asked to complete a questionnaire encompassing questions on their asthma characteristics, the AKT, ACT, API as well as questions on patients’ attitude towards asthma medication and emergency treatments.

#### Asthma Knowledge Test (AKT)

The AKT is a questionnaire assessing asthma knowledge and self-management skills regardless of disease severity [8]. This questionnaire is particularly suitable for quality assurance and evaluation of asthma education programs. It encompasses four subdomains including knowledge regarding pathology (7 items), drug treatment (15 items), self-management (25 items) as well as non-drug interventions (7 items). The maximum score is 54. Since the AKT is not a fixed instrument, it must be adapted to current guidelines. Consequently, two of 56 items were removed and thus the version applied in the current study consists of 54 questions. Furthermore, the original version includes the answer options “correct” and “incorrect” [8]. In order to reduce the proportion of unanswered questions, the additional answer option "don't know" was included after consultation with the authors.

#### Asthma Control Test (ACT)

The ACT is a validated, frequently used questionnaire to evaluate symptom control of patients with bronchial asthma [9]. Patients will answer five questions regarding symptoms during day and night, the use of emergency medication, as well as self-assessment of asthma control over the past four weeks. The maximum score is 25. Depending on the achieved sum score, patients’ asthma will be classified into well controlled, poorly controlled and very poorly controlled.

#### Autonomy Preference Index (API)

The API assesses patients’ preference regarding information (8 items) as well as involvement in medical decisions (6 items) [10]. Each item uses a five-point scale with the lowest preference scored 1 and the highest preference scored 5. Sum scores will range from 0 to 100, with 100 corresponding to the strongest possible desire for information as well as involvement in medical decisions. The API was translated into German and was validated [14].

#### Attitude towards asthma medication

In order to assess the attitude towards medication for bronchial asthma, eight statements on drug therapy will be evaluated by the patient, given in Table 1. The following options are available for assessing the statements: (1) "Strongly disagree", (2) "Some of the time", (3) "Most of the time", (4) "Strongly agree". If one of the drugs mentioned in the statements was not prescribed, the statement is marked by the patient with (0) "Drug was not prescribed" (see Additional file 2). The items are summed up accordingly.

**Table 1 Tab1:** Statements of the questionnaire regarding attitude towards asthma medication

Statements	
1	I use the reliever spray every day.
2	I use the reliever spray no more than twice per week.
3	I take inhaled corticosteroids every day.
4	I take inhaled corticosteroids when needed.
5	I use a combination inhaler every day.
6	I use a combination inhaler when needed.
7	I take as little asthma medication as possible, even if I have asthma symptoms.
8	I manage my asthma symptoms well in everyday life.

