### Aims and Outcomes

This cluster randomized controlled trial (cRCT) aims to investigate the effectiveness of the eAEP compared to usual care in terms of 1) asthma knowledge, 2) asthma control, and 3) emergency treatments including the following endpoints:Baseline-adjusted difference in the number of correctly answered questions in the AKT [8] between intervention and control groupsprimary endpoint: after the eAEP (two weeks after study inclusion) and fAEP (twelve weeks after study inclusion), respectively.secondary endpoint: three months after the eAEP (three months after study inclusion) and fAEP (six months after study inclusion), respectively.secondary endpoint: at the end of the study (six-month follow-up).

Further secondary endpoints include:2)Baseline-adjusted difference in the total sum score obtained in the asthma control test (ACT) [9] between intervention and control groupsthree months after the eAEP (three months after study inclusion) and fAEP (six months after study inclusion), respectively.at the end of the study (six-month follow-up).3)Difference in frequency of emergency treatments (inpatient and outpatient treatments of asthma) between intervention and control groups at six months.

This trial further examines the relation between asthma knowledge and 4) patient autonomy as well as 5) attitudes towards asthma medication including the following endpoints:4)Correlation between the total sum score achieved in the autonomy preference index (API) [10] at the time point baseline assessment and the change in correctly answered questions in the AKT after the eAEP and fAEP, respectively.5)Correlation between the total sum score obtained in the questionnaire on attitudes towards asthma medication at the time point baseline assessment and the change in correctly answered questions in the AKT after the eAEP and fAEP, respectively.

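### The attitude-to-medication total sums opposed statements without reversal and counts a drug not prescribed as 0, so secondary endpoint 5 would partly reflect prescribing rather than attitude

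*Protocol article*

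**What the plan says.** Under Measurements, in the section on attitude towards asthma medication, "eight statements on drug therapy will be evaluated by the patient, given in Table 1". The answers are coded "1) 'Strongly disagree', (2) 'Some of the time', (3) 'Most of the time', (4) 'Strongly agree", with the same codes for every statement. Where a drug named in a statement is not part of the patient's treatment, "the statement is marked by the patient with (0) 'Drug was not prescribed". The section refers to Additional file 2 for this and then says "The items are summed up accordingly".

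In Table 1, statements 1 to 6 form three pairs, one for each drug class: reliever, inhaled corticosteroid and combination inhaler. The reliever pair sets "I use the reliever spray every day" against "I use the reliever spray no more than twice per week". The other two pairs set daily use against use when needed. Statement 7 concerns keeping medication to a minimum despite symptoms, and statement 8 concerns coping well day to day. Neither names a particular drug.

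Under Aims and Outcomes, endpoint 5 is a "Correlation between the total sum score obtained in the questionnaire on attitudes towards asthma medication" at baseline and the change in the asthma knowledge test (AKT). The Statistical analysis section plans a Spearman or Pearson coefficient for it. The article mentions no reverse coding, no sub-scores and no separate handling of the 0 code.

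**The concern.** A sum score orders patients only if a higher code means more of the same thing on every item. Here the two statements of each pair carry the same sign although they describe opposite behaviour, so agreement with one offsets disagreement with the other. Declaring one end of the scale favourable does not repair this, because the conflict lies within each pair.

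The 0 is a second and separate problem. It records that an item does not apply, but in a sum it counts as an answer one step below strong disagreement. The total then tends to rise with the number of drug classes prescribed.

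What is at stake is the reading of endpoint 5. The Background section expects education to improve medication adherence, and this endpoint is meant to relate attitude to knowledge gain. A correlation with the raw total, or the lack of one, could come in part from prescribing rather than attitude.

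**Working it through.** The article gives no range or worked value for this score, so there is no figure to reproduce. The check applies the printed rule.

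**Inputs (attitude section and Table 1).** Eight items; codes 1 to 4; 0 on both items of a class that is not prescribed; total = sum of the eight codes. Items 7 and 8 are taken as always answered 1 to 4.

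**Step 1: one pair.** If the pair is answered consistently, as x and 5 − x, it adds x + (5 − x) = 5 for any x. With d classes prescribed and all pairs consistent, the total is 5d + item 7 + item 8. Nothing from items 1 to 6 about how the drugs are used is left in it.

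**Step 2: two patients.** Both are prescribed a reliever and an inhaled corticosteroid, and answer items 7 and 8 alike (1 and 4).
- Reliever seldom, corticosteroid daily: 1+4+4+1+0+0+1+4 = 15.
- Reliever daily, corticosteroid when needed: 4+1+1+4+0+0+1+4 = 15.

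With all three classes prescribed, the eight answers (1,4,4,1,4,1,1,4) and their exact reverse (4,1,1,4,1,4,4,1) both total 20.

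**Step 3: the 0 code.** Take the profile (1,4,4,1,4,1,1,4), total 20, and set items 3 and 4 to 0 because that class is not prescribed. The total becomes 15, although no other answer has changed.

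**Step 4: attainable range.** The minimum is 2d + 2 and the maximum 8d + 8.

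| Classes prescribed (d) | Attainable range | Range if all pairs are mirrored, 5d + (2 to 8) |
|---|---|---|
| 0 | 2–8 | 2–8 |
| 1 | 4–16 | 7–13 |
| 2 | 6–24 | 12–18 |
| 3 | 8–32 | 17–23 |

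**Step 5: how strongly the total follows prescribing.** This depends on prescribing rates and answer patterns that the article does not give, so it was simulated under assumptions. There were 200,000 patients with answers drawn evenly from 1 to 4, unrelated to prescribing. The reliever was prescribed to 90%. The inhaled corticosteroid and combination inhaler were either prescribed independently at 50% each or were mutually exclusive at 45% each. The fixed score reverses one item of each pair (and item 7, purely for illustration), drops the 0s and takes the mean of the applicable items. Ranges run over the two prescribing patterns.

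| Quantity | Pairs mirrored | All items independent |
|---|---|---|
| Share of variance explained by number of classes, raw sum | 0.64–0.86 | 0.39–0.67 |
| Same, fixed score | 0.00 | 0.00 |
| Correlation with the daily-corticosteroid item among those prescribed it, raw sum | about 0.00 | 0.27–0.36 |
| Same, fixed score | 0.60–0.65 | 0.38–0.42 |

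The zeros for the fixed score follow from the simulation setting, in which answers are unrelated to prescribing. They show that the scoring rule no longer creates the link. They do not show that real attitudes are unrelated to treatment.

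**The case against.** The strongest reply is that the scoring may be complete elsewhere. The sentence on summing says that it is done accordingly, just after a reference to Additional file 2, which is not among the documents, and item direction is a detail often left to the questionnaire file. A recoding there is possible. But the article does more than leave the matter open: it prints common codes, a 0 and a sum, and endpoint 5 uses that total. For the Autonomy Preference Index the same article does say what a high score means. The printed rule is therefore faulty as it stands, and any recoding in the file would need to be reconciled with it.

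Other parts of the reply stand and limit the point:

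- Exact cancellation needs mirror-image answers. The labels mix agreement with frequency, so exact mirroring is not assured. With independent answers the loss is modest, as the last two rows of the simulation table show.
- A reader might infer that items 7 and 8 are also opposites. The article does not show this: a patient can keep medication low and still report coping well. Steps 1 and 4 do not rely on it.
- A reader might infer that fewer prescribed classes always means a lower score. It does not, because the attainable ranges overlap: 4–16 with one class and 8–32 with three.
- The simulated variance shares rest on prescribing rates that no part of the article gives.

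**Conclusion.** The point holds for the scoring rule as printed. Opposite patterns of use can get the same total, fully so when pairs are answered as mirror images and partly otherwise, and the attainable range is set by the number of drug classes prescribed. These two results are arithmetic and need only the printed codes and items 7 and 8 answered 1 to 4. The share of variance due to prescribing is illustrative: 0.39 to 0.86 under the assumptions stated.

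A reader might go further and conclude that the correlation in endpoint 5 could not be interpreted at all, or that the trial's main result is in doubt. The documents support neither. The raw total can keep some information on attitude, and it enters one secondary correlation only. It is not used in the mixed models of Table 2, in the emergency-treatment analysis or in the sample size. The point is worth correcting because the correction is almost free, but its reach is small.

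**What to change.** Before analysis, write a scoring rule for endpoint 5:

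1. State the direction of each item. Which behaviour counts as favourable, and how items 7 and 8 are oriented, is the sponsor's decision.
2. Reverse-score the items that run against that direction (5 minus the response).
3. Treat 0 as not applicable, not as a score.
4. Correlate the mean of the applicable items, instead of the raw sum, with the change in the AKT.

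If Additional file 2 already sets out such a recoding, correct the sentence on summing in the attitude section so that the two agree. The cost is a few lines in the analysis plan. The codes described in the article are enough to compute the new score, so data collection as described there need not change.

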#### Emergency treatments

In order to record emergency treatments due to asthma attacks, patients will answer two questions. These include the number of inpatient as well as outpatient emergency treatments over the past six months.

#### Patient questionnaire two weeks after study inclusion (t_*1*_)

All patients will receive a questionnaire by mail two weeks after study inclusion. Patients in the intervention group will be asked to complete the AKT again after they have completed the eAEP. Patients in the control group will also receive the AKT after two weeks, even if no fAEP has been attended by this time. Thus, it will be assessed whether they have already acquired knowledge about the disease independently of a fAEP using other sources such as the internet. In addition, patients from general practice in the intervention group will be asked about their internet use in general and whether they had participated in a fAEP in addition to completing the eAEP.

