All patients with asthma will be informed about the study and informed consent will be obtained. Patients from general practices in the intervention group will receive free access to the eAEP and will be asked to complete the eAEP within the following two weeks. Patients from general practices in the control group will receive usual care including a referral to a practice of pulmonology or a certified general practice for structured fAEP. Patients will be required to attend the fAEP within twelve weeks. As part of the baseline assessment, patients will complete a questionnaire including questions on their asthma characteristics, current medication and emergency treatments within the past six months. In addition, a structured questionnaire including the AKT, ACT and API as well as questions on patients’ attitude towards asthma medication will be handed out (further details on the questionnaires are depicted in the section ‘Measurements’). Furthermore, current lung function parameters will be extracted from patient chart or spirometry will be performed to assess lung function in terms of FEV_1_ and FEV_1_/FVC. Two weeks after study enrolment, all patients will receive the AKT by mail to complete the questionnaire again. After completion of the eAEP (three weeks after inclusion) or fAEP (twelve weeks after inclusion) patients will attend a follow-up consultation in the general practice in order to review the asthma knowledge gain as well as to discuss any open issues. In order to ensure adherence to the second appointment, all patients will be contacted via phone by an employee of the Institute of General Practice and Health Services Research at the Technical University of Munich. As part of a follow-up, patients in both groups will be contacted again by mail after three as well as six months and asked to complete a questionnaire comprising the AKT, ACT, API as well as questions on the attitude towards asthma medication. In addition, at the six-month follow-up, participants will be inquired to answer questions about emergency treatments. A detailed overview of the course of the present trial can be seen in Fig. 1.

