#### Statistical analysis

Descriptive statistics are used to describe the data included for the statistical analysis and are reported as the mean, standard deviation, median, quartile and ranges as well as absolute and relative frequencies. The primary endpoint is the asthma knowledge gain after the eAEP (two weeks after study inclusion) and fAEP (twelve weeks after study inclusion), respectively. A confirmatory hypothesis test for difference between intervention and control group is performed by a linear mixed-effects model at a two-sided 5% significance level. Based on the intention-to-treat principle, all patients will be included in analysis. The baseline value (number of correctly answered questions in the AKT at baseline), time since eAEP/fAEP, and group allocation (intervention or control group) will be used as fixed effects. Cluster effects of the general practices will be included in analyses as random intercepts. As previously mentioned, missing data for this variable will be imputed by performing a worst-case-analysis. Thereby, the average knowledge gain for drop-out patients is expected to be 0 points in the intervention group and 10 points in the control group. A comparison of the asthma knowledge gain between intervention and control group will also be made three months after completion of the eAEP (three months after study inclusion)/fAEP (six months after study inclusion) and at the end of the study (six-month follow-up). Similar calculations will be applied for the secondary outcome asthma control (difference in the achieved sum score of the ACT three months after completion of the eAEP/fAEP as well as at the six-month follow-up) (see Table 2). Emergency treatments as a secondary outcome will be considered binary in the analyses (0: No; 1: Yes, at least one emergency treatment). Due to the consideration of measurement repetition as well as data grouped in clusters, generalized estimating equations (GEE) will be applied. Group allocation is used as a covariate. Spearman or Pearson correlation coefficients will be calculated for the relation between 1) patients’ autonomy preference and asthma knowledge as well as between 2) patients’ attitude towards asthma medication and asthma knowledge. All analyses will be conducted exploratively with and without imputation in terms of a worst-case-analysis.

**Table 2 Tab2:** Overview of primary and secondary endpoints of the respective outcomes for linear mixed-effects models

			Time point (t)	

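### The intervention arm's primary AKT is requested after eAEP completion rather than at a fixed two weeks, so unfinished patients return it late or not at all

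*Protocol article*

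**What the plan says.** The Protocol article describes the two-week mailing twice. Study design attaches no condition: "Two weeks after study enrolment, all patients will receive the AKT by mail to complete the questionnaire again". The section on the two-week questionnaire (t1) also mails the form to everyone, but then treats the arms differently. For the intervention arm: "Patients in the intervention group will be asked to complete the AKT again after they have completed the eAEP". For the control arm: "Patients in the control group will also receive the AKT after two weeks, even if no fAEP has been attended by this time".

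Under Statistical analysis, "The primary endpoint is the asthma knowledge gain after the eAEP (two weeks after study inclusion) and fAEP (twelve weeks after study inclusion), respectively". The intervention arm's t1 form is therefore its primary measurement. The control arm's t1 form is not; it serves to detect knowledge picked up elsewhere. The later AKT mailings also follow the calendar: "patients in both groups will be contacted again by mail after three as well as six months".

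On the analysis, "Based on the intention-to-treat principle, all patients will be included in analysis". Missing primary values are imputed: "the average knowledge gain for drop-out patients is expected to be 0 points in the intervention group and 10 points in the control group". The plan adds: "All analyses will be conducted exploratively with and without imputation in terms of a worst-case-analysis".

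**The concern.** In one arm the wording links the primary measurement to finishing the treatment. In the other arm the date alone triggers it. The text does not say what an intervention patient who is still unfinished at two weeks should do with the form. A patient who follows the sentence literally waits, and then returns the form late or never.

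Three things are at stake:

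- **Unreturned forms.** A score that could have been collected is replaced by an assumed zero.
- **Late forms.** These are not missing, so no imputation applies. They carry a post-completion score under a two-week label. Some may follow the three-week GP appointment, at which the programme's content is reviewed.
- **The analysis without imputation.** The intervention arm is reduced to patients who finished the eAEP, set against all responding controls.

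**Working it through.** **The plan's own figures (Sample size estimation).** Intervention gain: 0.80 × 20 + 0.20 × 0 = 16. Control gain: 0.80 × 5 + 0.20 × 10 = 6. Planned difference: 16 − 6 = 10. With SD 15, two-sided 5% and 80% power, the normal approximation gives 36 per group (an exact t-test gives 36.3, with 79.7% power at 36). Design effect: 1 + (5 − 1) × 0.10 = 1.4, and 2 × 36 × 1.4 = 100.8. The stated 36 and 100 reproduce. The 10-point difference already counts 20% of intervention patients at zero gain.

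**Inputs for the check.** From the plan: gain 20 after the eAEP, mean control gain 5, imputed gains 0 and 10. Assumed, because the documents give neither: a share q of 10 to 40% of intervention patients who have not finished and return no t1 form, and a true gain g of 0 to 10 points in those patients.

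**Formulas.**

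- Difference if every patient were measured: (1 − q) × 20 + q × g − 5.
- Without imputation: 20 − 5 = 15 for any q. Excess over the all-patient difference: q × (20 − g).
- Planned imputation, all controls observed: (1 − q) × 20 − 5. Error: −q × g.
- Planned imputation, the same share q of controls missing and set to 10: (1 − q) × 20 − [(1 − q) × 5 + q × 10]. Error: −q × (g + 5).

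| q | g | All-patient difference | Excess without imputation | Error, imputed, controls observed | Error, imputed, both arms missing |
|---|---|---|---|---|---|
| 10% | 0 | 13 | +2 | 0 | −0.5 |
| 10% | 10 | 14 | +1 | −1 | −1.5 |
| 20% | 0 | 11 | +4 | 0 | −1 |
| 20% | 10 | 13 | +2 | −2 | −3 |
| 40% | 0 | 7 | +8 | 0 | −2 |
| 40% | 10 | 11 | +4 | −4 | −6 |

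Across these assumptions the analysis without imputation overstates the difference by 1 to 8 points. The planned imputation is off by 0 to −6 points; the −6 requires controls to be missing at the same 40% rate.

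**Late forms.** The documents give no share or delay for these, so I put no figure on them. If the extra time raises the score, the direction favours the eAEP, and this happens inside the confirmatory analysis because a late value is an observed value.

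**The timing covariate.** The model adjusts for time since eAEP/fAEP. A patient who finishes late and fills in the form at once has a short time since the eAEP, just like a patient who finished on schedule. The covariate does not register the delay since inclusion, and it has no value for a patient who never finishes. The Intervention Group section states that website use is not documented, so completion can be known only by asking.

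**The case against.** The strongest reply is that the sentence merely describes the expected order. Patients are asked to finish within two weeks, the form is mailed to all of them at two weeks, and the Discussion assumes they have finished by then. The article is condensed and the actual cover letter is not shown. That reply stands in part: literal compliance is one reading, and the share of patients it affects is unknown. It does not explain why the text provides for unfinished education in the control arm and not in the intervention arm.

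A reader might infer four stronger things that the documents do not support:

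- **That only completers get the form.** The text contains no such restriction, and every intervention patient is mailed one.
- **That the two-week control form is the primary comparator.** The control primary value is set at twelve weeks. The asymmetry has to be argued from the three-month mailing, which also carries no attendance condition.
- **That unreturned forms bias the confirmatory test towards the eAEP.** They count as zero gain, while missing controls count as 10, so the effect is neutral or unfavourable to the eAEP.
- **That the intention-to-treat principle is abandoned.** All patients stay in the analysis as allocated, under a rule fixed in advance.

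It is also fair to say that the 1 to 8 points should not be read against the planned 10, which is a worst-case figure. The matching figure without imputation is 15.

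Two things are left standing. Imputation cannot correct a late form. It is also written for drop-outs, and the article does not say whether a patient who stays in the study without finishing counts as one.

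**Conclusion.** The point holds as a defect in how the primary measurement is requested. It does not show that the confirmatory result is biased by missing forms. For unreturned forms the confirmatory difference moves by 0 to −6 points, at the price of replacing collectable scores with zero. For late forms there is an unquantified shift, plausibly towards the eAEP, that the planned imputation does not reach. In the exploratory analysis without imputation the overstatement is 1 to 8 points, or 4 points (15 instead of 11) at 20% non-completion with zero gain. All these sizes rest on an assumed 10 to 40% non-completion, an assumed true gain of 0 to 10 points, and patients taking the instruction literally. The sample size is unaffected. The change is worth making because it is cheap and later analysis cannot recover scores that were never collected.

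**What to change.** Ask every intervention patient to complete and return the AKT at two weeks, whether or not the eAEP is finished. Add one item asking whether the eAEP was finished and on what date; the time-since-education covariate needs this too. Align the Study design section and the section on the two-week questionnaire so that both state the same unconditional request.

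The cost is a change of questionnaire and cover-letter wording, with no extra visit. The observed intervention mean may be lower in the analysis without imputation, because patients who have not finished will now contribute their real scores.
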